## Abstract

In summer 2017, the World Health Organization published 10 facts on asthma, which is known as a major non-communicable disease of high clinical and scientific importance with currently several hundred million people—with many children among them—suffering from air passages inflammation and narrowing. Importantly, the World Health Organization sees asthma as being underdiagnosed and undertreated. Consequently, much more efforts in clinical disease management and research need to be spent on reducing the asthma-related health burden. Particularly, for young approximately 6 months aged patients presenting recurrent bronchitic respiratory symptoms, many parents anxiously ask the doctors for risk prognosis for their children's future life. Therefore, we urgently need to reevaluate if the current diagnostic and treatment measures are in concordance with our yet incomplete knowledge of pathomechanisms on exacerbation. To contribute to this increasing concern worldwide, we established a multicentric pediatric exacerbation study network, still recruiting acute exacerbated asthmatics (children >6 years) and preschool asthmatics/wheezers (children <6 years) since winter 2018 in Germany. The current study that has a currently population comprising 176 study participants aims to discover novel holistic entry points for achieving a better understanding of the poorly understood plasticity of involved molecular pathways and to define biomarkers enabling improved diagnostics and therapeutics. With this study description, we want to present the study design, population, and few ongoing experiments for novel biomarker research.

**Clinical Trial Registration**: German Clinical Trials Register (Deutsches Register für Klinische Studien, DRKS): DRKS00015738.

## Introduction

“Asthma deaths will increase in the next 10 years if urgent action is not taken” (1). At this point, doctors are usually left empty-handed because no definite management guidelines are deduced, currently except few prevention measures to answer questions from expectant parents. The particular emphasis of current research is mostly captured on biomarker research, and some effort is directed toward the development of antibody therapeutics in adult asthmatics or autoimmune disorders (2). The asthma prevalence had increased dramatically from 3.6% in 1980 to 7.5% in 1995 and from 8.7% in 2001 to 9.3% in 2010 in children below 18 years (3–6). The prevalence in childhood is sex- and age-dependent, i.e., preadolescent male children have an increased risk of asthma symptoms and hospitalization rates compared with girls (7). Despite remarkable progress evolved from basic research, still, 338,000 people die every single year (1). Although the asthma prevalence is higher in childhood, the asthma-associated mortality rate is increased in adults (8). Nowadays, the main goal of care for patients with bronchial asthma is quality of life improvement, whereby many of them are excluded from this aid *de facto*. Unfortunately, many patients worldwide do not have access to the current standard of treatment, and the implementation of diagnostic and therapeutic measures can be hampered by the educational and social levels of the patients and their custodians. In part, the highest lethality rates are found in economically developing countries, suggesting that underdeveloped medical care drives the increased numbers of asthma fatalities (9). This high number challenges the view that inadequate medical care is the predominant cause of numerous fatalities. Clearly, there must be other important factors being causative for this high death toll (8).

Except for some scientifically accepted prevention measures, e.g., breastfeeding or farming in childhood, scientists and clinicians also focus on describing causes that may potentially have an impact on the pathogenesis of allergy and asthma (10, 11).

Furthermore, we will have to identify and precisely characterize the triggers responsible for recurrent asthma attacks of individual children with bronchial asthma manifestation. Are discrete trigger factors sufficient for an exacerbation, or do multifactorial causes contribute to an asthma attack? Is each asthma attack clinically and/or molecularly similar? How can we classify risk profiles for those patients? How can we draft personalized therapy suggestions to parents of affected children to prevent future attacks? The main reasons for choosing these trigger factors are to understand the molecular interaction between the triggering substances and the individuals.

The pathomechanisms involved during allergic sensitization have been previously studied in murine models, as described in the literature. This fostered our current understanding of this allergic disease. In particular, the first description of airway eosinophilia and the T helper 2 cell and the associated cytokines were initially described in murine models (12, 13). Murine models enable scientists to functionally analyze processes and mechanisms (14). Persson and colleagues have exemplarily observed that interleukin-1β is involved in lung neutrophilia and T helper 2 inflammation in virus-induced asthma exacerbations in an interleukin (IL)-1β^−/−^ mouse model (15). The deriving complex data provide interesting hypotheses, enabling us to get more detailed insights into relevant asthma pathomechanisms in humans (16, 17). But so far, unfortunately, these results are currently far from translation into clinical reality and personalized healthcare. With respect to affected individuals, particularly for children and adolescents, an extremely difficult clinical all-day problem is balancing packages of measures for appropriate prevention IL-therapy options. Such individualized expedient measures would be extremely desirable because many severe asthma attacks can put so much strain on the lung that the recovery takes several weeks, with scars left behind being very likely. In detail, patients with a severe asthma exacerbation present a prolonged recovery period. The recovery time and the responsiveness to the treatment are variable here (18). A prolonged recovery may be associated with decreased prognosis and increased morbidity. O'Byrne and colleagues have previously shown that severe asthma exacerbation is associated with a declined lung function (19). Exactly, these open problems must urgently be considered and be taken to our researcher's and clinician's hearts.

## Aims and Scopes

A major focus of our research is to gain insights into the environmentally triggered plasticity of the regulome in the nasal and bronchial epithelium—a portal of entry for many potential triggers of asthma and the epigenome of these cells as a probable molecular interface between the environment and genome interpretation. One of our main research projects is the analyses of non-coding RNA molecules (small interfering RNA, microRNA, medium, and large RNAs). To give an overview, Figure 1 summarizes the effects of extracellular trigger factors on the nasal and bronchial epithelium. The biogenesis of small interfering, medium, and large RNAs, which we also focus during our investigations, are not presented here. In detail, small non-coding RNA molecules will be holistically analyzed in the biomaterials (e.g., serum samples, nasal epithelial cells) of the cohort, and the interaction to the naso-/broncho-epithelium will be enlightened to figure their role as targets in experimental cell culture models. Our laboratory has previously established a special miR-specific isolation protocol in cooperation with the colleagues from Paris/France, which allows us to analyze all miRs in one sample through the next-generation sequencing (NGS) method. Weil et al. (2017) previously described in detail each methodological step for the microRNA characterization from biomaterials (21). In addition, we have established an adenovirus-vector system for functional analyses of the selected non-coding RNA molecules. The exposure of risk factors and the influence on exacerbation and course will be analyzed in *in vitro* models. Subjects will not undergo any interventions or allergic exposure. To implement this idea, we established an organotypic three-dimensional (3D) cell culture model of primary human nasal and bronchial epithelial cells from numerous healthy and affected study participants where these vectors can be validated. Furthermore, we will analyze these targets-of-interest in mouse models where gene therapeutic techniques, e.g., CRISPR/Cas will be used to knock-down the molecule-of-interest to present the affected signaling pathway. Here, we will also use *Dermatophagoides pteronyssinus* extracts to mimic a somewhat exacerbation model *ex vivo*. Furthermore, the effect of *D. pteronyssinus* on virus infection and on cell integrity will be tested. This project is still under publication. Here, subject-derived biomaterials are essential to perform *in vivo*-like experiments. Our major focus will be the exploitation of potential biomarkers for diagnostic use, which may possibly open new sources for therapeutic regimens in the near future.

**Figure 1 F1:**
[figure not shown]
Respiratory epithelium is a gateway for “biocode” research. Respiratory epithelium is constantly connected to environmental factors. Different trigger factors can lead to epigenetic changes. Gene regulatory molecules, i.e., microRNAs, are small non-coding RNA molecules with a length of 21–23 nt, which regulate gene regulation posttranscriptionally (20). Their role and the role of siRNAs and medium and large RNA molecules as potential biomarkers will be analyzed. Experimental design of ongoing experiments to define biomarkers for clinical and therapeutic implementation. This figure was created with BioRender.com.

Descriptively, observed results derived from human samples will be proven in at least cell culture models to establish their clinical and biological connection and highlight their importance for clinical routine (22–24).

Next, the microbial and fungal role of the airway epithelium in nasal and pharyngeal swabs will be explored to highlight potential preventive strategies. Through the NGS method, we will analyze the 16-S and 18-S rRNA in the nasal and pharyngeal swabs of the entire cohort to analyze the microbiome and fungiome levels of exacerbated subjects. A detailed description of the method is currently in publishing, and the details will be shared upon request. With this methodology, we will be able to observe bacteria or fungi where their cultivation with traditional culturing techniques is not possible. Furthermore, we will also start to collaborate with the asthma study network in Greece to compare here phenotype changes between the two countries.

Another focus will the exploitation of the role of IL-33 on regulatory B cells and memory B cells. Co-culture experiments will highlight this functional connection and the influence of IL-33 *in vitro*.

Then, cytokine and chemokine analyses in different biomaterials, e.g., serum, plasma, and induced sputum, will show whether an acute exacerbation is associated with specific “cytokiome” levels and whether their release can be used as potential laboratory exacerbation parameter in clinical routine. The additional biomaterials, particularly sera/plasma and cells obtained from the study cohort, may support the idea of translational research to establish biomarkers for early diagnosis of exacerbation and rapid treatment to reduce morbidity and mortality. The experimental results will be compared by correlation analyses with the clinical item parameters obtained from the questionnaires. The listed network partners (including life scientists and physicians) are clinically and experimentally experts in their area, and the methods are appropriated to implement these research questions into praxis. Most of the described projects have been done or will be performed soon.

In summary, the main focus of our clinical and experimental work is to detect new phenotypes and endotypes, evaluate developed biomarkers and to identify new biomarkers, to uncover the functions of individual cells during an exacerbation, and to decipher the characterization of the microbiome and its role during exacerbation.

Due to the significance of this extraordinary study design and population and the currently performing analyses on the biomaterials with the emphasis on different clinical and molecular levels will present comprehensive insights into the molecular “barcodes of asthma,” which might contribute to improving our understanding of relevant common and individual pathomechanisms, and as such may serve as a highly relevant example for implementation the idea “from patient to bench and from the bench back to the children's hospital” to provide a potential clinical and therapeutic translation.

## Methods and Analysis

To counteract to this concern, we have built a clinically prospective, multicentered, observational exacerbation cohort to provide deeper insights. Starting in winter 2018, we have now established a pediatric exacerbation network in Germany. The study recruitment is currently ongoing, up to date having already recruited 176 study subjects having chronic bronchitis/wheezing episodes (age group <6 years, *n* = 62), children and adolescents with bronchial asthma (age group >6 years, *n* = 55) presenting recurrent asthma attacks, as well as healthy children, adolescents, and adults (*n* = 59). Currently, our biomaterial collection comprises approximately 2,500 specimens, including sera, plasma, cells, swabs, and sputum.

The study cohort comprises two diseased groups (acute exacerbated wheezers and asthmatics) and healthy children and adults. The subjects will not undergo any interventional/allergic provocations.

The inclusion criteria for subjects with asthma are based on international recommendations, including lung function parameters (25), a gestational age over 37 weeks with an inconspicuous peripartal/postnatal period, and presenting an acute asthmatic attack at study enrollment. The definition of subjects with a wheeze is based on previously published data (26–29), including a history of at least two obstructive bronchitis episodes and acute wheezing at study enrollment, as well as an inconspicuous peripartal/postnatal period. Patients (chronic bronchitis and asthmatics) suffering from acute wheezing, respiratory illness, dyspnea, chest tightness, etc. (acute respiratory symptoms) were classified as “exacerbators.” The recruitment of wheezers is clinically and scientifically promising because underlying mechanisms of whether wheezers will develop chronic asthma are not sufficiently understood. Epigenetic signatures/environmental factors are likely to play important roles in disease development and persistence of symptoms (30, 31). We aim to analyze similarities between wheezers and asthmatics to make the diagnosis at the early stages of the disease and to discover potential biomarkers for the clinical routine. Moreover, subjects with no chronic diseases or chronic medication and an inconspicuous neonatal period were classified as healthy controls (age range: 3 months to 65 years of age). The healthy pediatric controls will be age- and sex-matched with diseased children (preschool asthmatics/wheezers and asthmatics). The recruitment of healthy adults will be helpful for correlation analyses of age-dependencies. In the future, we are also planning to include adult asthmatics. This is currently in consideration with the entire study members.

All individuals will be observed on the basis of two follow-up (FU) visits to recognize how the “active” and “non-active” phases are presented and differ, respectively (Figure 2).

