**Questionnaire (summarized item parameters)**
i. Age and sex at study enrollment
ii. Place of birth, mode of birth, gestational weeks, birth height and weight
iii. Postnatal complications, including infections, mechanical ventilation
iv. Duration of breastfeeding
v. Vaccination
vi. Pet owner
vii. Allergic symptoms including itch, rhinitis, conjunctivitis, and duration of allergic symptoms
viii. Atopic eczema
ix. Family history for atopic disorders
x. Recurrent respiratory symptoms at preschool period
xi. Chronic medication and the response to this medication
xii. Asthma control test score
xiii. Current symptoms (e.g., cough, chest tightness, wheezing, and fever)

The study recruitment started in January 2018 and will be finished on 31/12/2021. All patients with typical symptoms requiring study enrollment will be presented at the emergency room of the (affiliated) university children's hospitals, and a study enrollment protocol will be obtained. Participating study centers are Center of Child and Adolescent Medicine, Helios University Hospital Wuppertal of Witten/Herdecke University, Germany and Children's Hospital, and Helios Hospital Niederberg, teaching hospital of University Hospital Essen/Germany. All participated subjects and/or their parents/legal guardians provided written informed consent. Healthy controls will be recruited mostly from children of teammates of the study centers, or the following alternatives may be considered for the recruitment of healthy children and adolescents, e.g., calls in social platforms, flyers for day-care centers, schools, private practices, social institutions, newspapers, and internet. These announcements will be separately reported to the ethics committees in advance.

A patient stratification in subgroups (atopic vs. non-atopic, transient vs. seasonal-dependent vs. multi-triggered vs. single-triggered vs. permanent wheezers, steroid-independent or steroid-dependent phenotypes) were based on clinical (questionnaire) and laboratory parameters (e.g., immunoglobulin E) (32).

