All analyzed biomaterials and data involving human participants are in accordance with ethical standards and with the Helsinki declaration (1964) and its later amendments or comparable ethical standards. Ethical approval and later amendment approvals are obtained by the Ethics Committees of Witten/Herdecke University and Ärztekammer Nordrhein, and the study is registered at the German Clinical Trials Register (DRKS). All experiments, including the data extraction and analyses, were and will be obtained pseudonymously. The obtained subject-relevant information and biomaterials were and will be separately coded with study-relevant numbers and codes. All subject-relevant data and experimental results will be filled in a database to perform correlation analyses. With this coding strategy, except the (deputy) study head, nobody may follow retrospectively to patient-sensitive information. All biomaterials were processed according to established internal standard operating procedures and were stored at −80°C or in liquid nitrogen until experimental use. The study recruitment is still ongoing, and the current subject and biomaterial numbers allow first pilot experiments and statistical analyses. The description of the collected data will be done on the basis of statistical parameters. Insofar as the distribution of the data enables, the comparison of the two groups will be carried out using analyses of variance and typical significance tests. Data will be presented as box plots with medians, interquartile ranges, minimum–maximum values or standard deviation, or standard error of the mean. In addition, the data will be presented and analyzed by heat maps, cluster analyses, point clouds, bar, and column charts. Moreover, sequencing results will be normalized within each group, and normalization methods, e.g., DeSeq2, will be performed as previously described by Anders and Huber (33). In addition, metagenomic and proteomic data will be analyzed by professional biostatisticians within our study network. The raw data will be uploaded on separate repository databases, as stated by the journal's requirements. For the experiments, age- and sex-matched stratification will be done between diseased and healthy groups in which each diseased patient will be compared with the same healthy children based on age and sex.

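### Healthy controls are free of chronic medication by rule and patients are not, so diseased-healthy differences balanced only on age and sex mix disease with any controller treatment

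*Protocol article*

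**What the plan says.** All of this stands in the Methods and Analysis section of the protocol article.

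- **Controls.** The eligibility paragraph states that "subjects with no chronic diseases or chronic medication and an inconspicuous neonatal period were classified as healthy controls".
- **Asthmatics.** Besides a diagnosis by international recommendations with lung function, they need "a gestational age over 37 weeks with an inconspicuous peripartal/postnatal period, and presenting an acute asthmatic attack at study enrollment". No medication limit is given.
- **Wheezers.** They need "a history of at least two obstructive bronchitis episodes and acute wheezing at study enrollment" and an unremarkable perinatal history. Again no medication limit is given.
- **Medication data.** Table 1, item xi, collects "Chronic medication and the response to this medication".
- **Subgroups.** The text after Table 1 lists several patient strata, among them "steroid-independent or steroid-dependent phenotypes) were based on clinical (questionnaire) and laboratory parameters", with immunoglobulin E as the example of a laboratory parameter.
- **Comparison.** The statistics paragraph says that "age- and sex-matched stratification will be done between diseased and healthy groups" and that "each diseased patient will be compared with the same healthy children based on age and sex". The group comparison "will be carried out using analyses of variance and typical significance tests", where the distribution allows. No factor other than age and sex is named for this contrast.

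Aims and Scopes also plans to correlate experimental results with the questionnaire items. Advantages and Pitfalls does not list medication among the limitations.

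**The concern.** Exposure to long-term drugs is zero among controls by definition and unrestricted among patients. A marker that responds to controller treatment but not to disease will therefore differ between the groups, in the direction of the drug effect. Matching on age and sex leaves this untouched.

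The study looks for biomarkers, phenotypes and endotypes in nasal epithelial cells, nasal and pharyngeal swabs, induced sputum, serum and plasma. Several of these come from the airway itself, where a locally acting drug could leave a signal. Findings from human samples are then to be taken into cell culture and mouse experiments. A treatment signature read as a disease signature could thus set the targets for that later work.

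A related question arises for the steroid subgroups. If they are in fact separated by current steroid use, a molecular difference between them may be produced by the drug.

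**Working it through.** **Step 1: the structure.** This needs no figures.

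| | Controls | Wheezers and asthmatics |
|---|---|---|
| Chronic medication | Excluded | No stated limit; recorded in item xi |
| Balanced between groups | Age, sex | Age, sex |

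Let *f* be the share of patients on a controller and *d* the drug's effect on a marker, in SD units. With no disease effect, the expected diseased-healthy difference is *f* × *d*. It is zero only if *f* or *d* is zero. Item xi and the steroid-dependent subgroup imply that *f* is not zero.

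Adding medication as a covariate brings no extra information on disease. Since no control is treated, the disease term is then estimated from untreated patients against controls, which is the stratified comparison in another form.

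**Step 2: the group sizes.** The article reports 62 wheezers, 55 asthmatics and 59 healthy subjects: 62 + 55 + 59 = 176, which reproduces its total. It gives no sample size calculation, power, treated share or drug effect.

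**Step 3: an illustration.** Assumptions, none from the article: SD 1, two-sided alpha 0.05, normal approximation, *d* from 0.3 to 0.8, *f* from 25% to 100%.

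- Difference = *f* × *d*
- SE = √[(1 + *f*(1 − *f*)*d*²)/n₁ + 1/n₀]
- Chance of significance = Φ(diff/SE − 1.96) + Φ(−diff/SE − 1.96)

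Worked case, 55 asthmatics against 59 controls, *f* = 0.5, *d* = 0.5: difference 0.25; SE = √(1.0625/55 + 1/59) = 0.190; ratio 1.31; chance of significance 25.9%, against a nominal 5%.

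Chance that a marker unrelated to disease is significant, 55 v 59:

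| Treated share | *d* = 0.3 | *d* = 0.5 | *d* = 0.8 |
|---|---|---|---|
| 25% | 6.8% | 10.1% | 17.9% |
| 50% | 12.5% | 25.9% | 53.6% |
| 75% | 22.3% | 50.7% | 87.4% |
| 100% | 36.0% | 76.0% | 99.0% |

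For all 117 patients (62 + 55) against 59 controls at *d* = 0.5, the rates are 12%, 34%, 64% and 88% down the same column.

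The 59 controls include adults, and only paediatric controls are matched to patients. At present recruitment the matched number is below 59, so these rates are upper-end for each pair of assumptions. The bias *f* × *d* does not depend on sample size.

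**Step 4: the steroid subgroups, conditionally.** If the split follows current steroid use, the whole of *d* falls on the contrast. For 55 asthmatics split evenly, SE = √(2/27.5) = 0.270, and a pure drug effect of 0.3, 0.5 or 0.8 SD is significant in 20%, 46% or 84% of comparisons. If the split rests on something else, these figures do not apply.

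**Step 5: the effect of the fix.** Among untreated patients *f* = 0, so the drug part of the difference is zero and the false-positive rate returns to 5%. The number of such patients is not given.

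**The case against.** The strongest reply is that a healthy control is ordinarily untreated, that nothing in the article contradicts itself here, and that covariates and sensitivity analyses normally belong in a fuller plan that is not shown. Medication is recorded, correlations with questionnaire items are planned, and a steroid-independent stratum is named, which may come close to an untreated group.

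Part of this stands. The control definition is ordinary and need not change, and an unseen plan may handle medication. But the article does state its comparison rule, and that rule balances age and sex only. Correlating markers with questionnaire items does not take the drug component out of the group difference. The steroid strata are not tied to the diseased-healthy comparison.

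Three stronger readings are tempting and are not supported:

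- **That the steroid-dependent subgroup is defined by being on steroids.** The article cites questionnaire and laboratory parameters and gives no rule. Item xi also covers response to medication, so the class could rest on response or need.
- **That false significance is known to be high.** The rates above rest on an assumed treated share and drug effect, and on all 59 controls.
- **That every contrast is compromised.** The wheezer-asthmatic comparison and the active versus non-active comparison across visits do not use the medication-free controls, so this rule does not affect them.

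It is also fair to object that untreated patients are probably milder. Requiring a marker to hold in that stratum before calling it disease-related could discard true markers of severe disease. The fix therefore sets no such requirement.

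**Conclusion.** The point holds for the diseased-healthy comparison. To the extent that patients take controllers, that comparison mixes disease with treatment, and the stated age and sex balancing cannot remove the mixture. That some patients do so is a sound inference from item xi and the named subgroup; how many is not stated.

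The size is therefore open. Under the assumptions shown, the spurious difference runs from 0.075 SD (25% treated, 0.3 SD effect) to 0.8 SD (all treated, 0.8 SD effect). At 55 v 59 this gives 6.8% to 99% false significance, upper-end because the matched paediatric control number is smaller. The width of that range shows that the magnitude cannot be settled from the article.

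For the steroid subgroups the conclusion is conditional: it applies only if they are separated by current steroid use. The change is worth making because it costs little and bears directly on what may be called a disease marker.

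**What to change.** 1. In the statistics paragraph, add to the comparison rule that the diseased-healthy comparison is reported separately for patients without and with steroid controllers, by item xi. Both strata are set against the same age- and sex-matched paediatric controls, with the age and sex balance checked again in each stratum.
2. Report the number of patients in each stratum.
3. Describe a marker seen only in the on-controller stratum as possibly treatment-related.
4. State that the untreated stratum is smaller and probably milder, so that absence of a marker there does not rule out a link to severe disease.
5. State how the steroid-dependent and steroid-independent subgroups are defined. If current steroid use separates them, do not read molecular differences between them as endotypes without noting that the drug may produce them.
6. Add background medication to the limitations.

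The cost is a few sentences and one stratified analysis on data already collected, with less precision in each stratum. It assumes that the full form of item xi, shown only in summary in Table 1, identifies steroid controllers. No change to eligibility, treatment or sampling is needed.
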